#### Objective 2b: Examine the Effectiveness of SSBC

All clients will complete in-person measurements (weight and waist circumference) at baseline, 12-, and 24-month post program. At locations with an appropriate space (ie, walking track), cardiorespiratory fitness will also be assessed via a 6-minute walk test [79]. In addition, all clients will complete surveys at baseline, session 6, 12, and 24 months post program via REDCap (Research Electronic Data Capture). Surveys will assess self-reported T2D status (12- and 24-months only [80,81]), moderate-to-vigorous PA, dietary intake, and health-related quality of life (EQ-5D-5L) [82]. Table 3 outlines the measures that will be used in the evaluation of SSBC effectiveness. Using an equity-focused lens, a prospective cohort subsample of clients (n=1285) will be followed across 24 months to evaluate the differential impact of SSBC on T2D status, assessed by change in HbA_1c_, in addition to self-reported T2D status. All effectiveness outcomes will be analyzed using descriptive statistics. Hierarchical multivariable regression models will be used to assess the impact of SSBC on effectiveness outcomes, adjusting for potential confounders and accounting for within-subject and within-site clustering. Covariates (ie, sex, gender, and ethnicity) will be included to adjust for within-subject and within-site correlations. A sensitivity analysis using missing data imputation will be conducted to evaluate the potential impact of nonadherence on study outcomes. Data will be disaggregated to examine differences in effectiveness by ethnicity, socioeconomic status, municipality, sex, and gender within and between sites. For the subsample, a multilevel binary logistic regression will be used to examine differences in sociodemographic factors between those who do and do not experience a clinically significant reduction in HbA_1c_ at 24 months.

**Table 3 table3:** Overview of effectiveness measures and associated time points.

		Eligibility	Baseline measurement	Postprogram measurement	Follow-up measurements	
Measure		Online intake survey	Baseline on session 1	After session 6	12-month follow-up	24-month follow-up
Age		✓				
Current T2D^a^ diagnosis		✓				
Prediabetes diagnosis or ADA^b^ diabetes risk score		✓				

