**T2D status**						
	1-item self-report T2D status (in questionnaire)		✓		✓	✓
	Laboratory-based HbA_1c_^c^ (subsample)		✓		✓	✓

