#### Objective 2c: Examine the Cost-Effectiveness of SSBC

The cost-effectiveness of SSBC will be determined using organizational data collected in objective 2a and client-level costs. Health-related client-level costs will be detailed using the Health Resource Utilization Questionnaire [88] delivered in a survey. The Health Resource Utilization Questionnaire asks for specific details regarding health professional visits, admissions to the hospital, laboratory tests or investigations, and use of medications. On a per-client basis, costs will be assigned to health care resource use using a fully allocated hospital cost model (for in-patient costs) and provincial guides to medical fees (for outpatient costs) every 6 months to account for potential fluctuations in medical costs. The 5 dimensions of EQ-5D-5L will be converted into a weighted health state utility value that will provide weightings for quality-adjusted life years (QALYs) and Canadian conversion tariffs for transforming health state profiles into utility scores [90]. QALYs are calculated based on the quality of life of a person (measured using health state utility values estimated from the EQ-5D-5L) in a given health state and the time spent in that health state. Incremental cost per client and effects generated by SSBC will be assessed using a Canadian health care system perspective. The outcome of cost-effectiveness analysis is the incremental cost-effectiveness ratio, where incremental cost-effectiveness ratio=Δ Cost/Δ HbA_1c_ and is the incremental cost of SSBC delivery per client. The outcome of our cost-utility analysis is the incremental cost-utility ratio, where incremental cost-utility ratio=Δ Cost/Δ QALY [91].

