#### Recruitment and Consent

##### SSBC Clients

Recruitment strategies will vary across delivery sites, based on the local connections previously or newly established by the research team and delivery team. A series of generic recruitment materials (eg, posters, pamphlets, or social media posts) and potential recruitment pathways (eg, health assessment days and physician referrals) have been generated by the research team and will be shared with all delivery sites. These recruitment strategies will be included in the implementation strategies’ blueprint and toolkit. Each site will tailor their recruitment plan to the local contextual needs with support from the research team.

Interested or referred individuals will complete an eligibility survey to determine their eligibility for SSBC. Individuals are eligible for SSBC if they are 18 years of age or older, able to read and speak English, and meet one of the following criteria: (1) have been diagnosed with prediabetes by a physician, (2) have an HbA_1c_ of 5.7%-6.4%, (3) have an American Diabetes Association risk assessment score indicating high risk (≥5), or (4) have achieved T2D remission (have an HbA_1c_ of <6.5%) without any diabetes-related medications for a minimum of 3 months. Eligible individuals will be directed to an online consent form. Following completion, individuals will be scheduled for their first SSBC session at their local YMCA implementation site.

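### The HbA1c subsample's responder model reduces a repeated continuous outcome to yes/no and names no baseline HbA1c, so baseline differences between groups can look like differential benefit

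*Protocol article*

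**What the plan says.** All references are to the protocol article.

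- **Purpose of the subsample (Objective 2b).** For the equity question, "a prospective cohort subsample of clients (n=1285) will be followed across 24 months", with HbA1c change and self-reported T2D status as the two markers of T2D status. Table 3 places laboratory HbA1c at baseline, 12 months and 24 months.
- **Model assigned to it (Objective 2b).** The method is a multilevel logistic model with a yes/no outcome. Its stated target is "differences in sociodemographic factors between those who do and do not experience a clinically significant reduction in HbA_1c_ at 24 months". No threshold and no covariate list are given for this model.
- **Other models in the same section.** Hierarchical regressions cover the effectiveness outcomes in general, "adjusting for potential confounders and accounting for within-subject and within-site clustering". The covariate sentence reads "Covariates (ie, sex, gender, and ethnicity) will be included to adjust for within-subject and within-site correlations". An imputation sensitivity analysis and disaggregation by ethnicity, socioeconomic status, municipality, sex and gender are also planned.
- **Eligibility (SSBC Clients).** Any one of four criteria is enough. One is to "have an American Diabetes Association risk assessment score indicating high risk (≥5"), which needs no HbA1c value. The physician-diagnosis route also states none, and the remission route has only an upper bound (below 6.5%). Substudy entry is by expressed interest, with no HbA1c range.
- **Medication (Objective 2c).** The Health Resource Utilization Questionnaire asks about "use of medications". Table 3 schedules it at baseline, 12 and 24 months. Its stated use is costing.

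**The concern.** Whether a client reaches a fixed reduction depends on where that client starts. The Introduction uses HbA1c below 5.7% as the boundary of no longer having prediabetes. Someone already below it has little room for a meaningful fall, and someone with a high first reading is more likely to show one, partly through regression to the mean. If sociodemographic groups differ in starting HbA1c or entry route, a responder model without baseline HbA1c reports that difference as if the programme worked better in one group. Those group contrasts are what the substudy is for, and it deliberately oversamples by visible-minority status and male sex.

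Two further costs follow. The cut discards information and leaves the 12-month value unused. And since no rule is given for new T2D, a client who progresses, starts glucose-lowering medication and then falls past the cut would, read literally, be coded a responder.

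**Working it through.** The figure n=1285 cannot be reproduced, because the article gives no alpha, power, effect size, SD, responder rate or dropout. It is not disputed here. The HbA1c means, SDs, effects, cuts and progression shares below are assumptions.

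**1. Information kept after dichotomising.** For a normally distributed outcome cut so that a proportion p responds, relative efficiency is φ(z_p)² / [p(1−p)].

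| p | φ(z_p) | Efficiency |
|---|---|---|
| 0.50 | 0.399 | 0.159/0.25 = 0.64 |
| 0.20 | 0.280 | 0.0784/0.16 = 0.49 |
| 0.10 | 0.175 | 0.0308/0.09 = 0.34 |

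**2. Spurious odds ratio from the mix of starting levels.** Assumptions: true baseline 5.4 or 6.0 (SD 0.2); effect −0.2 only where the true value exceeds 5.7, the same in both groups; change SD 0.2; measurement SD 0.15; cut 0.3. Response is about 13% when observed baseline is below 5.7% and 38% otherwise. The reference group has 20% normal-range starters and 31.5% responders, so odds 0.315/0.685 = 0.460.

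| Comparison group, normal-range starters | Responders | OR |
|---|---|---|
| 20% | 31.4% | 1.00 |
| 30% | 29.6% | 0.420/0.460 ≈ 0.92 |
| 50% | 25.9% | 0.350/0.460 ≈ 0.76 |

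With a cut of 0.5 the ORs are 1.00, 0.92 and 0.75.

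**3. Spurious odds ratio from a shift in mean baseline.** Assumptions: N=1285; 31.3% in one group (the article's figure for the racialized share of the population); true baseline mean 5.75 (SD 0.33); reduction of 0.2 to 0.4 times the excess above 5.3; change SD 0.2; measurement SD 0.12; cut 0.3 or 0.5; single-level logistic model; 500 replicates. There is no group effect given baseline.

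| Baseline gap | OR without baseline | Rejections at nominal 5% | OR with baseline | Rejections |
|---|---|---|---|---|
| 0 | 0.98–1.00 | 4–6% | 0.98–1.00 | 3–7% |
| 0.1 | 1.13–1.28 | 10–40% | 0.91–0.95 | 6–7% |
| 0.2 | 1.28–1.62 | 32–97% | 0.86–0.92 | 8–14% |

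Here the group that starts higher looks more responsive. Adding observed baseline HbA1c removes most of the artefact but over-corrects somewhat, because the baseline reading contains measurement error.

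**4. Medicated progressors.** Share of cohort = progress × medicated × fall past the cut.

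- Low: 0.05 × 0.3 × 0.3 = 0.45%, about 6 of 1285.
- High: 0.15 × 0.6 × 0.6 = 5.4%, about 69 of 1285.
- With 20% genuine responders, they would be 0.0045/0.2045 = 2% to 0.054/0.254 = 21% of all those coded as responders.

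**The case against.** The strongest reply is that the article already plans something better. The hierarchical models cover effectiveness outcomes, Table 3 lists HbA1c among the effectiveness measures, and accounting for clustering within subjects implies repeated measures. On that reading the responder model only profiles responders alongside a continuous analysis. This stands in part. A reader might infer that the logistic model is the sole inferential analysis of the subsample, or that clients without a 24-month draw are simply dropped. The text supports neither: the hierarchical models may include HbA1c, and imputation is planned as a sensitivity analysis. The information loss in step 1 therefore applies to the responder model, not necessarily to everything done with HbA1c. But the article does not say that the hierarchical HbA1c model leads on equity, and the only model it ties expressly to the subsample is the binary one.

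A reader might also infer that baseline HbA1c is excluded. The article does not say so. The logistic model's covariates are unlisted, and a fuller plan may add it. The point is that baseline HbA1c is not named, while eligibility makes it matter. Naming it would still leave the dichotomy.

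On medication, a reader might apply the Introduction's 70% progression over 10 years: 1 − 0.3^(2/10) = 21% in 24 months, and from there a sizeable share of false successes. That rate is for people with prediabetes, whereas the cohort may include normal-range starters. The calculation also assumes a constant hazard and no programme effect, and the medication shares are not in the documents. T2D status is followed as a separate outcome, so progression is not hidden.

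Finally, restricting the responder model to baseline HbA1c of 5.7% or more would remove clients whom the programme deliberately enrols. That stands, so the restriction belongs in a sensitivity analysis.

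**Conclusion.** The point holds as a weakness in the stated analysis. The responder outcome depends on starting HbA1c, eligibility permits normal-range starters, and the model's description names nothing to separate starting level from programme benefit. Whether this distorts the results depends on how far groups differ at baseline, which is not reported. The bias is nil with equal baselines. In the illustrations it reaches an OR of 0.76 with a large imbalance in normal-range starters, or 1.62 with a 0.2-point shift in mean baseline. These figures show direction and plausible scale; they are not estimates for this trial. The loss of information follows from the dichotomy itself, given approximate normality and the responder rate. Miscoding of medicated progressors is secondary, uncertain and probably small. Severity: should fix, with moderate confidence.

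**What to change.** 1. State in Objective 2b that the lead equity analysis of the subsample is the hierarchical (mixed) model of continuous HbA1c at baseline, 12 and 24 months, with time-by-factor interactions for the sociodemographic factors and entry route as a covariate. Entry route should also interact with time, so that it adjusts change as well as level.
2. Keep the responder logistic model as secondary, with its threshold stated and baseline HbA1c as a covariate. Note that adjustment for a single measured baseline can over-correct slightly.
3. Add two sensitivity analyses of the responder model: one limited to baseline HbA1c of 5.7% or more, and one counting self-reported new T2D or newly started glucose-lowering medication as non-response.

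The cost is wording and analysis code; laboratory HbA1c, T2D self-report, medication use and the eligibility information are already collected. The downside is that the headline becomes a mean difference rather than a responder proportion. There is time to settle it: Results reports 89 first blood draws, and delivery ran from May 2024 to November 2025, 18 months, so no client could yet have reached the 24-month draw.

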**T2D status**						
	1-item self-report T2D status (in questionnaire)		✓		✓	✓
	Laboratory-based HbA_1c_^c^ (subsample)		✓		✓	✓
**Client questionnaire**						
	Demographic characteristics		✓			
	GLTEQ^d^ [83]		✓	✓	✓	✓
	PAV^e^ [84]		✓	✓	✓	✓
	4-item 24-hour movement measure (adapted for SSBC^f^ urban scale up in line with Canadian 24-hour movement guidelines [85])		✓	✓	✓	✓
	Brief Food Frequency Measure [86]		✓	✓	✓	✓
	Self-compassion [87]		✓			
	EuroQol-5D-5 level HRQOL^g^, Weighted Health State Utility Value [82]		✓	✓	✓	✓
	HRU^h^ [88]		✓		✓	✓
	General program feedback (7 items created for SSBC: scored on a scale of 1=extremely dissatisfied to 7=extremely satisfied)			✓		
	Program acceptability (8-item theoretical framework of acceptability [73])			✓		
	Net promoter score (1-item)			✓		
	Membership (1-item)			✓		
	Referral (3-items)			✓		

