	**Reach**												
		Number of individuals interested in SSBC^g^ but do not sign up, number of clients enrolled in SSBC, and number that withdraw after enrollment	Client		REDCap^h^ audit of eligibility survey		Number of delivery staff interested, trained, and retained as SSBC coaches			C and SL		Annual report and monthly meetings (SL and RRC); virtual coach training platform tracking	
		Demographic characteristics of clients	Client		Client survey		Recruitment strategies reaching participant			Client		Client eligibility survey	

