## Results

Program implementation within each region is occurring in a phased approach, with partners beginning program delivery in 1 site (2024-2025) before expanding to any additional locations (2025-2027). Program enrollment occurs continuously during the implementation phase across all sites. From May 2024 to November 2025, a total of 13 delivery sites began program delivery (1 regional YMCA decided to launch in 3 sites at once), 722 participants have enrolled in the program, and 406 have begun the program (153/342, 44.7% non-Western or Eastern European, 17/342, 5% of whom report identifying as Indigenous; 80/345, 23.2% men or 82/347, 23.6% male). Further, 334 participants have expressed interest in the substudy, of which 89 have had their first blood draw (19/89, 21.8% identify as a visible minority; 4/89, 5.3% indigenous; 16/82, 19.5% men or 16/81, 19.8% male). An additional 13 sites have confirmed they will launch the program in 2026.

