### Strengths and Limitations

Sustainable DPP scale-up is a necessary condition for improved population health outcomes. This is the first study to examine how to sustain an evidence-based DPP in real-world community contexts. Unlike other DPPs that have been delivered at a national scale (eg, US National DPP [94] and English National DPP [95]), SSBC was designed to include characteristics that are key for achieving sustainability—for example, being brief, adaptable, community-based, and delivered by laypersons with no specialized training. By exploring the underlying factors underpinning the dynamic processes of implementation and sustainability when delivered at a broad scale, and engaging early with municipality partners to develop and prioritize sustainability planning to overcome identified barriers, this research will discern best practice implementation determinants, outcomes, and strategies critical for sustaining DPP implementation across Canada and beyond.

Implementation science is critical in improving health equity by ensuring health programs are accessible and effective to those most in need [40,41]. Of the participants that have enrolled thus far, we are on track for reaching an ethnically representative sample of the Canadian population, which will allow us to understand if SSBC is effective for visible minorities; however, individuals self-identifying as men and male continue to be underrepresented in SSBC participation. Establishing buy-in from health care professionals in clinical settings may help us to reach this demographic, but developing partnerships with this sector has proven challenging. Extending diabetes prevention to community settings is key to advancing health equity; however, staff shortages and turnover are ongoing challenges faced when working with community partners.

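### Client demographics are scheduled only at session 1, so reach cannot be described by ethnicity, sex, gender or socioeconomic status for clients who enroll but never start

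*Protocol article*

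**What the plan says.** Table 3 (Objective 2b) separates an online intake survey at eligibility from the next column, "Baseline on session 1". The row "Demographic characteristics" is ticked only in the session 1 column. The intake column is ticked for age, current diabetes diagnosis, and prediabetes diagnosis or risk score.

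Table 1 lists two client-level indicators under Reach. One is a set of counts that includes "number of clients enrolled in SSBC, and number that withdraw after enrollment", taken from an audit of the eligibility survey. The other is the demographic profile of clients, taken from the client survey.

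The Recruitment and Consent section gives the order of steps: eligibility survey, online consent form, then scheduling of the first session.

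The Results report that "722 participants have enrolled in the program, and 406 have begun the program". The demographic figures are attached to those who began: "153/342, 44.7% non-Western or Eastern European, 17/342, 5% of whom report identifying as Indigenous" and "80/345, 23.2% men or 82/347, 23.6% male".

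The Discussion, under Strengths and Limitations, then says: "Of the participants that have enrolled thus far, we are on track for reaching an ethnically representative sample of the Canadian population".

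**The concern.** Reach is one of the four implementation outcomes in Objective 2a, and the Introduction presents scale-up as a way to reach Canadians at risk equitably. The reach counts start at enrollment, but the demographics needed to break those counts down start at session 1. Clients who leave between the two are counted without being described on ethnicity, sex, gender or socioeconomic status.

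This bears on a decision the team already faces. The Discussion reports that men remain underrepresented and looks to health care professionals to reach them. If demographics exist only for starters, the data cannot show whether men do not sign up, or sign up and then do not start. The two problems call for different remedies. The same holds for racialized clients.

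The Discussion also describes the ethnic mix of enrolled participants, while the figures in the Results belong to a subset of starters.

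**Working it through.** **Inputs (Results section).** Enrolled 722; begun 406; ethnicity reported for 342, of whom 153 are in the non-Western or Eastern European group; gender reported for 345 (80 men); sex reported for 347 (82 male).

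**The article's own percentages.** 153/342 = 44.7%, 17/342 = 5.0%, 80/345 = 23.2%, 82/347 = 23.6%. All match the text.

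**Enrolled but not begun.** 722 − 406 = 316, and 316/722 = 43.8%. The session 1 schedule can leave at most these clients without demographics.

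**Begun, but no reported ethnicity.** 406 − 342 = 64, and 64/406 = 15.8%. Gender is unreported for 406 − 345 = 61 starters and sex for 406 − 347 = 59. These clients had reached session 1, so its timing does not explain the gap.

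**Total without reported ethnicity.** 722 − 342 = 380, and 380/722 = 52.6%. Of these, 316/380 = 83.2% had not begun and 64/380 = 16.8% had.

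**How far the 44.7% can be carried.** The limits below set every client with missing ethnicity first outside the group, then inside it.

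| Population | Lower limit | Upper limit |
|---|---|---|
| 406 who began | 153/406 = 37.7% | (153 + 64)/406 = 53.4% |
| 722 enrolled | 153/722 = 21.2% | (153 + 380)/722 = 73.8% |

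These are arithmetic limits, not plausible estimates. They show that the reported data constrain the mix among starters moderately and the mix among all enrolled clients very little.

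**Which comparisons remain possible for non-starters.** Under Table 3, age and diabetes or risk status. Under Table 1, also the recruitment strategy that reached the client, which comes from the eligibility survey. Ethnicity, sex, gender and socioeconomic status have no scheduled collection before session 1.

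**The case against.** The strongest objection is that Table 3 is an overview of effectiveness measures, not an inventory of the intake survey. Its intake column is visibly incomplete. Table 1 says the eligibility survey also records how the client was recruited, and the eligibility criteria require information on English and on diabetes remission; none of these has a row in Table 3. Table 2 places consent, intake survey and questionnaires together under baseline. The full survey may therefore already ask about sex or ethnicity, and no statement in the article says these data are absent for the 316. This stands as a reason for caution. It does not remove the point: where the article does place demographics, it places them at session 1 (Table 3) and in the client survey rather than the eligibility survey (Table 1), and the Results give demographics only for starters.

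A second objection is that no comparison of starters with non-starters is promised. Objective 2a plans descriptive analysis, with representativeness judged against people with prediabetes in Canada. That is correct, and the question is not a named aim. It follows from setting the two reach indicators side by side under an equity aim.

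A third objection is that the Discussion sentence only says the study is on track and goes on to effectiveness in visible minorities, for which starters are the relevant group. The smaller denominators are also printed openly. This softens the criticism, but the sentence is still worded about enrolled participants.

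**Conclusion.** The point holds in limited form. As scheduled, clients who enroll but never start have no ethnicity, sex, gender or socioeconomic data, so reach cannot be described on those factors at the enrollment-to-start step. At the November 2025 snapshot, 316 of 722 (43.8%) stood at that step. The Discussion statement on enrolled participants rests on 342 of 406 starters.

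Stronger readings are tempting but not supported:

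- A reader might attribute all 380 missing ethnicities to the schedule. It can account for at most 316; the other 64 had begun, and the article gives no reason for their missing data.
- A reader might treat the 316 as clients who never start. Enrollment is continuous, so some may be waiting for a first session.
- A reader might conclude that nothing can be said about non-starters. Age and diabetes or risk status are collected at intake.
- A reader might infer that most loss occurs at this step. The article gives no completion or post-start withdrawal counts to compare it with.

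The conclusion assumes that Tables 1 and 3 reflect the actual forms, and that enrolled means having completed online consent, which the article does not define.

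**What to change.** 1. Move the existing demographic block (ethnicity, sex, gender, socioeconomic items) to the online step directly after consent and before session 1 is scheduled. If the intake survey already captures these items, correct Table 3 and use them.
2. Send the same REDCap block to clients who have enrolled but not started.
3. Check why 64 starters have no reported ethnicity, because moving the block may not solve that.
4. Report reach as consented, started and completed, each by sex, gender and ethnicity.
5. Limit the Discussion statement on ethnic mix to starters with data (342 of 406).

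This is a cheap improvement. It moves a form that already exists and adds no visit or procedure. The costs are a slightly longer online sign-up and a minor ethics amendment. It is best done before the 13 further sites launch in 2026, because data never requested from clients who leave before session 1 may not be recoverable later.

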### Intervention

SSBC aims to empower individuals with prediabetes to make long-lasting diet and PA changes. Trained SSBC coaches meet with clients for 6 one-on-one sessions focused on PA, reducing intake of added sugar, improving carbohydrate choices, and preventing relapse, with each session followed by supervised aerobic exercise. Coaches use a motivational interviewing-informed approach to bolster client autonomy. The core components of the SSBC program can be found in Textbox 1, and specific behavior change techniques are published elsewhere [62].

The core components of Small Steps for Big Changes.

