**Delivery site senior leadership**																	
	Consent and demographics											✓					
	Meeting minutes																
	Interviews											✓		✓			
	Site focus groups													✓		✓ (x2)	
	Municipality partners^j^: focus group													✓			
	Regional research coordinator: interview													✓			
	Diabetes prevention research group project manager: interview													✓			

^a^SSBC: Small Steps for Big Changes.

^b^These interviews will occur 2-3 months after the client has completed Small Steps for Big Changes.

^c^Site focus groups focused on creating sustainability models if deemed appropriate and identifying implementation strategies used.

^d^ORQ: Organizational Readiness Questionnaire.

^e^BISS: Behavioral Interventionist Satisfaction Survey.

^f^AIM: Acceptability of Intervention Measure.

^g^IAM: Intervention Appropriateness Measure.

^h^FIM: Feasibility of Intervention Measure.

^i^Coaches must have had 10 clients complete the Small Steps for Big Changes before being interviewed. Note that quantitative measures at 10 clients are to be completed ahead of the interview.

^j^Municipality partners include patient partners, Small Steps for Big Changes alumni, and persons with lived experience.

In addition, the multilevel factors posited to influence intervention implementation and use of implementation strategies (ie, the implementation determinants) will be examined across multiple settings and contexts. This information will be captured qualitatively through monthly meetings between the research team and delivery sites and through one-on-one interviews with 2 coaches at each site, site leads (after 1 year of delivery), and senior leadership at each site (after 2 years of delivery). Interview guides will be guided by the CFIR [67] to understand the contextual factors, organizational factors, processes factors, implementer characteristics, and intervention characteristics that impact implementation.

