Quantitatively, organizational readiness will be assessed at baseline [70] through surveys with site leads and coaches. Implementer satisfaction with the program will be captured using the Behavioral Interventionist Satisfaction Survey [71] and the Intervention Acceptability, Appropriateness, and Feasibility [72] measures during the delivery process. Client receptivity and satisfaction will be assessed quantitatively using the 8-item Theoretical Framework for Acceptability [73], a 7-item overall program satisfaction measure, and the 1-item net promoter score [74]. In addition, client interviews will be conducted with a purposive subsample (2-3 clients per site) post-SSBC completion to assess client satisfaction and acceptability. Program costs will be captured through monthly invoices and annual reports from sites.

Quantitative data from adoption, reach, dose, fidelity, program cost, and client and coach receptivity measures will be analyzed descriptively. Client demographics will be used to assess representativeness relative to people with prediabetes across Canada. SSBC program sessions will be audio-recorded using tablets with data saved on the University of British Columbia’s secure data research network in real-time; 2 program sessions per year from each coach will be randomly sampled and coded using an abbreviated version of the validated Motivational Interviewing Competency Assessment [75]. Motivational Interviewing Competency Assessment scores will be used to assess coach counseling fidelity, as done previously [57]. All implementation strategies used will be identified and classified according to definitions from the Expert Recommendations for Implementing Change project [76].

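### Client acceptability is scheduled only at or after the end of the program, with no stated collection from clients who stop early, so it describes completers and may overstate acceptability among all starters

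*Protocol article*

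**What the plan says.** The Intervention section sets the length of the program: "Trained SSBC coaches meet with clients for 6 one-on-one sessions". The column headed after session 6 in Table 3 is therefore the end of the program.

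In the client questionnaire block of Table 3, three items measure how clients received the program:

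- a single question on whether the client would recommend it, listed as "Net promoter score (1-item"
- a seven-question satisfaction measure written for this trial, with answers rated from 1 to 7
- a published scale of eight questions, listed as "Program acceptability (8-item theoretical framework of acceptability [73"

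Each has one tick, in the after-session-6 column. None is repeated at 12 or 24 months.

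For interviews, the text of Objective 2a says that "client interviews will be conducted with a purposive subsample (2-3 clients per site) post-SSBC completion to assess client satisfaction and acceptability". Footnote b of Table 2 adds: "These interviews will occur 2-3 months after the client has completed Small Steps for Big Changes".

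Table 1 names these surveys and interviews as the sources for client satisfaction and acceptability. Early leaving is tracked elsewhere in Table 1: Reach includes the "number that withdraw after enrollment", Dose delivered records sessions attended, and Program cost includes completion. No acceptability item is attached to any of these.

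On who is surveyed, Objective 2b says that "all clients will complete surveys at baseline, session 6, 12, and 24 months post program via REDCap".

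**The concern.** Someone who attends two sessions and does not return may have found the program unsuitable, or may have left for an unrelated reason. Acceptability data exist partly to tell these apart. As scheduled, the scales are tied to a session that this client never reaches, and the interviews are closed to the client by rule.

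Acceptability is a named implementation determinant. Objective 3a uses data from objectives 1 and 2 for the reports to each YMCA that inform the sustainability models, including which components continue and at what intensity. If those reports present completers' views as clients' views, a site could conclude that the program suits its community when part of that community left without being heard. Counts of withdrawals show that people left, but not why. Analysis cannot repair this later, because the data would not have been collected.

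**Working it through.** The plan gives no figure for client acceptability, so there is nothing to reproduce. The check has two parts.

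**1. Who can contribute acceptability data under the stated schedule**

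| Source | When | Stated for clients who stop before session 6? |
|---|---|---|
| 7-item feedback, 8-item acceptability, net promoter score (Table 3) | After session 6 only | Not stated; tied to a session they do not attend |
| 12- and 24-month surveys (Table 3) | Follow-up | Contain none of these items |
| Client interviews (Objective 2a; Table 2, footnote b) | 2-3 months after completion | No, completers only |
| Site focus groups that include clients (Table 2, footnote c) | From 24 months | Purpose is sustainability models and implementation strategies, not acceptability |

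Restriction to completers is explicit for the interviews. For the scales it is inferred from the column. At 2-3 interviews per site over the 44 planned sites, the interviews number 2 × 44 = 88 to 3 × 44 = 132, all with completers.

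**2. How large the difference could be**

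Let c be the share of starters who complete, S_c the satisfaction among completers and S_n the satisfaction among the rest.

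- Satisfaction among all starters = c × S_c + (1 − c) × S_n
- Overstatement if the completer figure is read as that of all starters = (1 − c) × (S_c − S_n)

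All three inputs are assumptions. Take S_c = 90%, S_n = 50%, 70% or 90% (no gap), and c = 60%, 75% or 90%:

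| c | All starters, S_n = 50% | Overstatement | All starters, S_n = 70% | Overstatement | S_n = 90% |
|---|---|---|---|---|---|
| 60% | 74% | 16 points | 82% | 8 points | 0 |
| 75% | 80% | 10 points | 85% | 5 points | 0 |
| 90% | 86% | 4 points | 88% | 2 points | 0 |

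Example: 0.60 × 90 + 0.40 × 50 = 54 + 20 = 74, and 90 − 74 = 16.

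The same formula on the other scales, with 10% to 40% of starters not completing:

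- A gap of 0.5 to 2 points on the 7-point scale gives 0.1 × 0.5 = 0.05 to 0.4 × 2 = 0.8 points.
- A gap of 20 to 60 in net promoter score gives 0.1 × 20 = 2 to 0.4 × 60 = 24.
- With no gap, both are 0.

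The Results section cannot supply c. Of 722 enrolled, 406 had begun, so 722 − 406 = 316 (43.8%) had not. Enrollment is continuous, so some of these are simply waiting to start, and the number who finished is not given.

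**The case against.** The strongest reply is that the survey half rests on inference. Objective 2b refers to all clients and to REDCap, and a REDCap survey can be sent to someone who has stopped attending. A journal article may leave the trigger or an exit survey to the full protocol. This stands in part: one cannot say that early leavers are asked nothing, only that no acceptability collection from them is stated. It does not help the interviews, where completion is a stated condition. Nor does it help the follow-up surveys, which omit the items.

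A reader might infer that acceptability is biased upward as a matter of fact. The article does not show that. It gives no scores by completion status and no reasons for leaving, and a result labelled as completers' acceptability is unbiased for completers. The error arises only if it is read as the view of all starters.

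A reader might also infer that the equity findings are compromised because the program will look equally acceptable in every group. That does not follow. The planned disaggregation by ethnicity, socioeconomic status, sex and gender concerns effectiveness, and completers' scores can still differ between groups.

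Finally, the consequence is limited. Client receptivity is analyzed descriptively, and attendance, completion and withdrawal are counted, so acceptability can be read beside attrition. Sustainability planning also draws on monthly meetings, coach and site-lead interviews, and focus groups. All of this stands and lowers the weight of the point. None of it supplies the views of those who left.

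**Conclusion.** The point holds in limited form and is minor. Following the stated schedule yields acceptability data from completers: explicitly for interviews, and by the natural reading of Table 3 for the three scales. Such data may overstate acceptability among all starters. An upward direction is plausible but not shown.

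The size is unknown. The illustration gives 0 to 16 percentage points of satisfaction, and depends wholly on assumed completion and an assumed gap. Completion will be known from the trial's own records; the gap will not be, unless some early leavers are asked. No effectiveness estimate, test or sample size is affected.

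**What to change.** This is a cheap improvement:

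- **Survey trigger.** Have REDCap send the feedback, acceptability and net promoter items to every client who attended session 1, at the earlier of session 6 or a fixed time after session 1. Use a short version for those who stopped.
- **Interviews.** Allow the purposive sample to include some non-completers across sites. A quota at every site is not needed: one of 2-3 interviews would take a third to a half of that site's completer interviews.
- **Reporting.** Report completers and all starters separately, with the number of starters and the response count. If nothing is collected from early leavers, label the results as completers only and give the number of starters beside them.

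The cost is an automated trigger and a change to the sampling rule, with no additional interviews. The downsides are a probably low response among those who left, so the all-starter figure would itself need cautious reading, and fewer completer interviews wherever some are reallocated. Thirteen sites had begun delivery by November 2025, 13 more were confirmed for 2026, and 44 are planned, so 44 − 13 = 31 planned sites could use the change from their first client.
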